### Blinding

Allocation is concealed from the study Principal Investigator and the study team at the time of the participants’ inclusion in the trial; however, field staff and the project coordinator collecting and managing the data will not be blinded to participants’ allocation. In no circumstances should the blinding be broken to the study team.

## Methods: data collection, management and analysis

### Data collection methods

Data on the outcome measures will be collected at four time points during the trial in accordance with the schedule depicted in Fig. 1. These are the baseline assessment during enrolment (T0); re-assessment after the completion of the intervention programme for the intervention arm and also for the controls (T1); re-assessment of the controls at the end of the intervention programme and the follow-up assessment of the intervention arm (T2); and follow-up assessment of the controls post intervention (T3).

#### Workplace environment scan

The workplace environment scan will be conducted by the senior social worker using the Moos Work Environment Scale (WES) [16]. Data will be collected during the briefing session through an online survey. Participants from each site will be asked to fill in the survey on site at the end of briefing session. Participants who have consented but miss out on the briefing session can contact the project team. They will be guided to fill in the baseline survey through a telephone call. Incomplete surveys will be identified during the data management process right after baseline data collection. Participants who have not completed the survey will be contacted via instant messaging or emails to encourage a re-attempt of the survey.

#### Outcome measures

Assessments on the outcome measures will be conducted at different time points in accordance with the time schedule tabulated in Fig. 2. Data on these outcome measures will also be collected using an online survey form. For baseline assessment, data will be collected at the same time as the workplace environment scan. Participants will be asked to fill in both surveys at the same time. All participants will be invited to provide their mobile telephone number on the form before commencing the survey. Since the mobile number will be used as the unique identifier for linking data collected at different time points, it would be important to ensure that they are correctly reported. With the permission of the participants, these mobile numbers will be verified with the records retained by their companies.

**Fig. 2 Fig2:**
[figure not shown]
Standard Protocol Items Recommendations for Interventional Trials (SPIRIT) figure. T0 baseline assessment during enrolment, T1 re-assessment after completion of the intervention programme for the intervention arm and also for the controls, T2 re-assessment of the controls at the end of the intervention programme and the follow-up assessment of the intervention arm, T3 follow-up assessment of the controls post intervention

### Data management

All hard copies from the study will be kept at the Research Office of Tung Wah College (TWC) located at [name]. All electronic files, including documents generated in the study and the electronic version of the signed consent form, the database developed for the study, and other data sets derived from the database, will be housed and stored in the secure file server designated for research at TWC. All electronic database and any data sets derived from the database will be password protected. The passwords will only be revealed to the key members of the research team and the statistician who will be handling the data for analyses. For further security, personal information provided by participants during enrolment will be kept in a separate database from the other data collected during the study. The only linkage between these databases is via the unique identifier – the mobile phone number provide by the participant. Hard copies of data will be securely stored in a locked file cabinet inside a secured office accessible only by a designated staff member through a security code. All data, both hard and soft copies, will be stored for 7 years.

### Confidentiality

Information on the participants and their responses to the survey will not be revealed to site managers or the Human Resources Departments of the companies. This will ensure that all identifying data can be managed in a confidential manner. Participants are free to withdraw from the study at any time without any request of a reason. Withdrawal of consent will not affect participants’ employment at their current work site (Additional file 2). However, participants will be informed that data that have already been collected may still be used in the analyses, and they will also be advised that it may not be possible to withdraw their data from the study results.

### Statistical methods

#### Statistical analysis plan

The analysis of the primary and secondary outcome measures will be conducted in accordance with the study design as a wait-listed cluster randomised trial and the nature of the variables. An intention-to-treat analysis will be applied to all primary and secondary outcomes. Any missing data will be imputed using the multiple imputation by chained equations approach. Should there be any differences identified between the intervention arm and the wait-list controls by comparisons of the baseline data collected, these variables will be considered potential confounders to be adjusted. A significance level of 5% will be adopted for testing all hypotheses.

The primary outcome measure of the study, namely MHL, will be analysed using a repeated-measures approach with possible adjustments to participants’ and sites’ characteristics. This will involve comparison of the mean change in the MHL scores from baseline to the completion of the intervention programme between the intervention and control groups (i.e. from T0 to T1). Since the study is a cluster randomised trial, the cluster sampling effect will be adjusted for. In order to cater for the sampling technique as well as the repeated measures of the outcome variable, the generalised linear latent and mixed model (GLLAMM) will be applied to test for any group differences.

For secondary outcome measures, the variables are of the same nature as for the MHL, namely continuous variables, and thus the approach of analyses will be the same. For the follow-up data, since all participants will receive the intervention programme, there will not be a distinction between the intervention and control groups and thus all participants will be considered a single group. Hence, the analysis will only focus on the changes in outcome measures across time. For the repeated measures of the outcome variables, a linear mixed-effect model will be applied.

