### Participant timeline

#### Sample size

For the sample size, it has been estimated that about 400 workers are required with an estimated effect size of about 0.5 units of a standard deviation difference in the MHL scores between the intervention and control arms [12]. The sample size calculation is based on this assumption with a power of 80% required to detect a true intervention effect at a type I error margin of 5% with an intraclass correlation of about 0.01 for the clusters. It is also assumed that 10% of participants will drop out of the project. Since groups of participants are recruited from different sites with an average size of about 20 workers, a total of 20 sites would be required.

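### With 20 randomised sites and no small-sample method stated, a GLLAMM test in its usual form would run somewhat above the nominal 5%

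*Protocol article*

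**What the plan says.** All quotes are from the protocol article.

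- **Primary test.** The Statistical analysis plan section compares the mean change in MHL score from T0 to T1 between arms. It promises an adjustment for clustering and states that "the generalised linear latent and mixed model (GLLAMM) will be applied to test for any group differences".
- **Level.** "A significance level of 5% will be adopted for testing all hypotheses".
- **Number of clusters.** The Sample size section concludes that "a total of 20 sites would be required", at about 20 workers each. It assumes "an intraclass correlation of about 0.01 for the clusters" and adds that "It is also assumed that 10% of participants will drop out of the project".
- **Randomisation.** The Allocation section makes the site the unit of randomisation, 1:1, stratified by three companies.
- **Type of outcome.** The Statistical analysis plan treats MHL and all secondary outcomes as continuous, and it already uses a linear mixed-effect model for the follow-up data.

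The article does not give the estimator, the reference distribution, the degrees of freedom or the random-effect structure for the GLLAMM.

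**The concern.** Information about the arm effect comes from 20 sites, 10 per arm, however many workers each contains. GLLAMM is ordinarily fitted by maximum likelihood (ML) with normal-theory tests. With few clusters this goes wrong in two ways: ML divides the between-site sum of squares by the number of sites rather than by its degrees of freedom, so the standard error is too small, and 1.96 is used where a t value on 18 degrees of freedom is 2.10.

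A second issue depends on how the model is built. When both waves are modelled, a random intercept for site appears equally at T0 and T1 and cancels from the change. A model with site and worker intercepts alone would contain a cluster term and still leave the tested contrast unadjusted for clustering. Site-level variation in the change is plausible here, because site managers are encouraged to act on the environment scan and the group session is held site by site.

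At stake are the 5% level of the primary test, and of the secondary tests that follow the same approach, and the width of their confidence intervals.

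**Working it through.** **The plan's own figure.** For 0.5 SD, two-sided 5% and 80% power, 63 workers per arm are needed before clustering. The design effect is 1 + 19 × 0.01 = 1.19. Then 2 × 63 × 1.19 / 0.9 = 166.6, or about 167 workers, not 400. This mismatch is a separate matter. The calculations below take the 20 sites as given.

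**Inputs.** J = 20 sites, 10 per arm. Analysed site size m = 20 × 0.9 = 18, so 360 workers. ICC ρ = 0.01 from the protocol; ρ = 0, 0.02, 0.05 and 0.10 are assumptions. The ICC is applied to the change score and the test is taken as two-sided; both are assumptions too.

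**Test statistic.** With total variance 1, let λ = mρ + (1 − ρ). The arm difference D has variance 4λ/(Jm). The between-site sum of squares SSB is distributed as λ times chi-square on 18 df (16 if company is fitted). ML estimates λ by SSB/20, or by the pooled variance when the between-site variance is estimated at zero. Reject when |D| / √(4λ̂/360) > 1.96.

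**Null simulation (400,000 to 1,000,000 runs per setting).** Rejection rates:

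| ICC | ML, z | ML, z, company fitted | REML, t on 18 df | t test on site means |
|---|---|---|---|---|
| 0 | 4.6% | 4.9% | 2.9% | 5.0% |
| 0.01 (protocol) | 5.7% | 6.3% | 3.7% | 5.0% |
| 0.02 | 6.5% | 7.4% | 4.2% | 5.0% |
| 0.05 | 7.6% | 9.1% | 4.8% | 5.0% |
| 0.10 | 7.9% | 9.8% | 5.0% | 5.0% |

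At ICC 0.01, the ML likelihood-ratio test gives 5.1% (5.7% with company), REML with z about 5.0%, and REML with Satterthwaite degrees of freedom about 4.3%.

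**Check on the upper end.** When the site variance is almost never estimated at zero, the ML z statistic equals a t on 18 df multiplied by √(20/18). The test then rejects when |t| > 1.96 × √(18/20) = 1.859, which has probability 7.9%. With company fitted, 1.96 × √(16/20) = 1.753 on 16 df gives 9.9%. Both agree with the last row.

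**Site intercept only.** The standard error of the change contrast then omits the design effect 1 + 17ρ. At a change-score ICC of 0.01 this is 1.17, and the error is 2 × [1 − Φ(1.96/√1.17)] = 2 × [1 − Φ(1.812)] = 7.0%.

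**Power at ICC 0.01, 0.5 SD, 180 per arm.** The non-centrality is 0.5/√(2 × 1.17/180) = 4.385. With 1.96 and a normal reference, power is Φ(4.385 − 1.96) = 99.2%. With 2.101 and a non-central t on 18 df it is 98.5%.

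**The case against.** The best defence is that the article names a class of models, not an estimator or a reference distribution. It promises an adjustment for clustering and rules out no correction. Such details are often left to a full protocol or SAP, which is not shown. At the protocol's own ICC the excess is about 0.7 percentage points; with a likelihood-ratio test it is about 0.1, and at ICC 0 the ML z test is conservative. REML with t on 18 df, at 3.7%, is further from 5% than the method it would replace.

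Most of this stands. It limits the size of the point and makes it conditional. It does not remove it, because the article fixes a named method for the confirmatory test, and that method in its usual form has no small-sample protection.

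Four stronger readings are tempting, and the documents do not support them:

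- **That the test certainly exceeds 5%.** The estimator and the reference distribution are not stated, so this can only be said of the usual form.
- **That the error favours the intervention.** The excess of a two-sided z test is symmetric, so false differences are as likely in either direction.
- **That the error reaches 15% or 23%.** Those values need an intercept-only model, which the article does not specify, together with change-score ICCs of 0.05 and 0.10, which it does not assume. An ICC near 0.10 would reproduce the 400 workers, but so would an effect near 0.32 SD, so the 400 is no evidence for a high ICC.
- **That the imputation ignores clustering.** The article says only "Any missing data will be imputed using the multiple imputation by chained equations approach". It does not say that the imputation is single-level.

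**Conclusion.** The point holds in conditional form. If the GLLAMM is fitted by ML with a normal reference, the two-sided type I error at the planned ICC of 0.01 is about 5.7%, or about 6.3% with company fitted. It rises to about 8% (about 10% with company) only under assumed ICCs of 0.05 to 0.10. If in addition only a site intercept were fitted, it would be about 7% at a change-score ICC of 0.01. These figures rest on equal site sizes of 18, normal outcomes and an ICC that applies to the change. The inflation is modest under the plan's own assumptions, but it is avoidable at almost no cost and should be removed.

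**What to change.** For the T0 to T1 comparison, replace GLLAMM with a linear mixed model fitted by REML with Kenward-Roger or Satterthwaite degrees of freedom. Put a random site effect on the T1 score adjusted for baseline or, if both waves are modelled, include a site-by-time random effect. Apply the same to the secondary outcomes. Support it with a site-level t analysis of change, which held 5.0% at every ICC tried, or with a permutation test of site allocation within company.

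The change needs new wording and standard software only. The mixed model is slightly conservative when the ICC is near zero: about 4.3% with Satterthwaite degrees of freedom and 3.7% with a fixed 18 df, both at ICC 0.01. Power at ICC 0.01 falls from about 99.2% to 98.5%.

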#### Intervention arm

Consenting participants nested in the sites that are randomised to the intervention arm will receive the intervention immediately (Fig. 1). The intervention will commence with a workplace environment scan. Results of the scan will be fed back to the manager of the site during a professional consultation session. The psychoeducation training programme will be implemented with all willing participants enrolled into the online modules and commencing the MHFA programme. Upon completion of the online modules by all participants at each site, a face-to-face session will be conducted on site at the workplace. At the end of the intervention programme, participants will then be re-assessed on the outcome measures (T1). The sites and participants in the intervention arm will be followed for another 3 months, with re-assessment conducted post follow-up (T2).

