#### Control group

Consenting participants randomised to the wait-listed control group will also complete the baseline data collection measures, as those in the intervention group, but will not have access to the training programme until participants in the intervention arm have completed the programme with the re-assessment of the outcome measures. It is anticipated that the intervention programme will be implemented in the control group within 3–4 months after the commencement of the programme in the intervention arm. The same procedures will be applied to the controls as in the intervention arm, with re-assessment of outcome measures, immediately prior to the intervention (T1), at the end of the intervention (T2), as well as at the follow-up re-assessment (T3).

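### The follow-up analysis pools the arms as one group although they are in different exposure states at T1 and T2, so depending on how time is coded it can show a gain while the effect fades, understate the fade, or give an uncontrolled change

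*Protocol article*

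**What the plan says.** The Statistical analysis plan section compares the arms on change from T0 to T1 for the primary outcome and takes the same approach for the secondary outcomes. For the follow-up data it reasons that, since everyone will receive the programme, "there will not be a distinction between the intervention and control groups and thus all participants will be considered a single group". It continues: "Hence, the analysis will only focus on the changes in outcome measures across time". The model is given in one sentence: "For the repeated measures of the outcome variables, a linear mixed-effect model will be applied". That section states no arm term, no exposure term and no re-alignment of time to programme start.

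The waves are defined in other sections:

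- Intervention arm: "At the end of the intervention programme, participants will then be re-assessed on the outcome measures (T1"); these sites are then "followed for another 3 months, with re-assessment conducted post follow-up (T2").
- Control group: outcomes are re-assessed "immediately prior to the intervention (T1), at the end of the intervention (T2), as well as at the follow-up re-assessment (T3").
- Data collection methods: T2 is the "re-assessment of the controls at the end of the intervention programme and the follow-up assessment of the intervention arm (T2"), and T3 is the "follow-up assessment of the controls post intervention (T3").

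**The concern.** After baseline, the two arms are never in the same exposure state at the same wave. A mean over both arms at T1 or T2 therefore mixes states, and its change from wave to wave depends partly on when controls receive the programme and not only on whether the effect lasts. Dropping arm also gives up the only randomised comparison available after T1, the between-arm difference at T2.

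What is at stake is how the follow-up results are read. The Background says that person-directed programmes tend to work for 6 months or less and organisation-directed ones for 12 months or beyond. The Intervention section encourages managers to go on improving the workplace during follow-up. A pooled curve that rises from T1 to T2 could be taken for a delayed organisational benefit when it only reflects controls completing the programme.

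**Working it through.** The protocol gives no figure for the follow-up analysis, so there is none to reproduce.

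**Inputs.** E = 0.5 SD is the immediate effect on mental health literacy (Sample size). Allocation is 1:1 (Allocation). The fraction f of the effect retained three months after the programme is not in the protocol; it is an assumption, shown from 1 to 0. Also assumed: the same E and f in both arms, equal retention, and no secular drift unless stated.

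**Step 1: exposure state and expected mean, relative to T0.**

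| Wave | Intervention arm | Control arm |
|---|---|---|
| T0 | untreated, 0 | untreated, 0 |
| T1 | just completed, E | untreated, 0 |
| T2 | 3 months after, fE | just completed, E |
| T3 | not assessed | follow-up, fE |

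**Step 2: time coded T0 to T3.** The pooled means are (E + 0)/2 = E/2 at T1, (fE + E)/2 = (1 + f)E/2 at T2, and fE at T3 (controls only).

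- Pooled T1-to-T2 change: (1 + f)E/2 − E/2 = fE/2.
- True change from end of programme to follow-up: fE − E = −(1 − f)E.
- Pooled raw T2-to-T3 change: fE − (1 + f)E/2 = −(1 − f)E/2.

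With E = 0.5 SD:

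| f | Pooled T1 | Pooled T2 | T3 | Pooled T1 to T2 | True end to follow-up | Pooled raw T2 to T3 |
|---|---|---|---|---|---|---|
| 1 | 0.25 | 0.50 | 0.50 | +0.25 | 0 | 0 |
| 0.8 | 0.25 | 0.45 | 0.40 | +0.20 | −0.10 | −0.05 |
| 0.5 | 0.25 | 0.375 | 0.25 | +0.125 | −0.25 | −0.125 |
| 0.25 | 0.25 | 0.3125 | 0.125 | +0.0625 | −0.375 | −0.1875 |
| 0 | 0.25 | 0.25 | 0 | 0 | −0.50 | −0.25 |

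The pooled T1-to-T2 change is positive for every f above 0. At f = 0 a complete loss of effect appears as a plateau.

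A small simulation agrees: 20 sites of 18 completers (20 workers less 10% dropout), ICC 0.01, assumed within-person correlation 0.5 or 0.7, 40 runs per setting, and a single-group mixed model with a person intercept. A significant T1-to-T2 gain appeared in 95–100% of runs at f = 0.8, 62–70% at f = 0.5 and 15–40% at f = 0.25. With 40 runs these percentages are rough: the standard error at 62% is √(0.62 × 0.38/40) ≈ 0.08.

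**Step 3: only T2 and T3 pooled.** The last column of the table applies. The sign is right, but the raw means show half the true fade. In the simulated model fitted to all waves, the T2-to-T3 change was about 0 at f = 0.8 (true −0.10) and −0.08 to −0.11 at f = 0.5 (true −0.25).

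**Step 4: time aligned to each arm's own programme.** The change from end to follow-up is −(1 − f)E: −0.10, −0.25 and −0.375 SD at f = 0.8, 0.5 and 0.25. Sign and size are right without drift. If scores drift by d over those three months through calendar or repeat-testing effects, the estimate becomes −(1 − f)E + d. A drift of +0.10 SD would hide the fade at f = 0.8; +0.25 SD would hide it at f = 0.5. The protocol gives no value for d.

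**Step 5: what the T2 between-arm contrast offers.** Intervention minus control at T2 is fE − E′, where E′ is the immediate effect in controls. Drift common to both arms cancels. If E′ = E, the contrast is −(1 − f)E. Otherwise fE − E′ = −(1 − f)E + (E − E′), so any difference between the arms in immediate effect enters one for one.

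**The case against.** The strongest reply is that the protocol uses the term follow-up relative to each arm's own programme: T2 for the intervention arm, T3 for controls. On that reading a single group is coherent, because everyone passes through before, end and follow-up, and Step 4 shows that fading is then recovered. Time coding is also a detail that an article may leave to an analysis plan not shown here. This stands in part: the false gain is conditional on coding time by T0–T3. However, the aligned scale is nowhere stated, and it still yields a before-after change with no concurrent control. The removal of arm, unlike the time coding, is stated outright.

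Four stronger readings are tempting and not supported:

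- That the efficacy result is biased. The primary and secondary comparisons from T0 to T1 keep the arms apart.
- That the stated reason is false. All participants are due to receive the programme; what fails is the step from there to pooling.
- That the control T0-to-T1 data go unused. They are the comparator in the primary and secondary analyses.
- That a stated durability objective is lost. The Objectives list none, the Primary outcome measure section ties efficacy to the end of the intervention period, and the protocol does not say that follow-up change will be reported as a programme effect.

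**Conclusion.** The point holds, at moderate severity, for the follow-up analysis only. Receipt of the programme by everyone does not justify removing arm when exposure state differs by arm at T1 and T2 and T3 is missing for one arm by design.

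The size depends on the reading. With T0–T3 coding, the direction can be wrong: +0.125 SD against −0.25 SD at E = 0.5 and f = 0.5. With T2 and T3 only, the raw means show half the fade. With programme-aligned time, the fade is right in the absence of drift but uncontrolled. All three leave the randomised T2 contrast unused. The retained fractions are illustrative; the positive sign under T0–T3 coding holds for any f above 0, given equal arms and no drift.

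**What to change.** Replace the single-group statement. Keep arm in the follow-up linear mixed model, with fixed effects for wave and for exposure state (untreated, just completed, 3 months after) and random effects for site and participant. Let the control T0-to-T1 period inform the time trend in this model as well.

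State that the T2 between-arm contrast is read as 3-month minus immediate effect only on the assumption that the immediate effect is equal in both arms. This needs saying because controls are expected to start 3–4 months later. Report control-only T3, and any pooled before-after change, as descriptive and not as evidence of efficacy.

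The cost is revised wording, a slightly more complex model and one added assumption. The data are already scheduled for collection, and the wording is best settled before the follow-up data are analysed.
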